### Trial objectives

This protocol is reported following SPIRIT guidelines [25] to facilitate the reporting of the trial results using CONSORT guidelines [25]. The primary aim of the trial is to evaluate the effectiveness of Sleep Ninja, a CBT-I smartphone application, in reducing insomnia symptoms in children aged 10 to 12 years experiencing sleep disturbance. Using a two-arm randomised controlled trial, Sleep Ninja will be compared to an active control condition to determine the effectiveness of the app for improving insomnia symptoms after 6 weeks of use (primary endpoint), at 3-months follow-up (secondary endpoint), and at 9-months follow-up (tertiary endpoint). Secondary outcomes will be evaluated which include symptoms of depression and anxiety as well as sleep quality and daytime sleepiness, relative to the control condition. Whether reductions in depressive symptoms are mediated by improvements in sleep will be investigated, and the potential mediating role of cognitive processes, including repetitive thinking, dysfunctional beliefs about sleep and pre-sleep arousal, on treatment effects will be explored. The emergence of new cases of MDD at the tertiary endpoint will also be explored.

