### Hypotheses

The primary hypothesis is that relative to the active control condition, participants who receive the Sleep Ninja app will show greater improvements in child-reported insomnia symptoms at 6-weeks post-baseline (primary endpoint). Secondary hypotheses include that relative to the control condition, participants who receive the Sleep Ninja app will show a greater reduction in symptoms of depression and anxiety, daytime sleepiness, and improved sleep quality at 6-weeks post-baseline (primary endpoint), and improvements in primary and secondary outcomes will be maintained at 3-months post-baseline. In line with previous studies, it is hypothesised that reductions in depressive symptoms will be mediated by improvements in insomnia symptoms. The number of MDD cases at 9-months post-baseline in both groups (tertiary endpoint) will be explored.

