### Measures of mechanisms

All potential mechanisms will be measured at all four assessments (baseline, primary, secondary, and tertiary endpoints) and explored as mediators of change.

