To determine whether improvements in depression are mediated by changes in sleep, an additional MMRM analyses will be conducted using depression symptoms as the outcome and including a 3-way interaction term (time × group × insomnia). Similarly, to explore other potential mediators of treatment effects, additional MMRM analyses will be used and include 3-way interaction terms (time × group × mediator).

A deidentified data set may be requested by emailing the study team. Release of the data will be decided on a case-by-case basis and at the discretion of the Chief Investigator and facilitated through a data repository using Research Data Australia.

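### The mediation hypothesis is tied to a time × group × mediator interaction, which tests moderation and not an indirect effect

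*Protocol article*

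**What the plan says.** Under Hypotheses, "it is hypothesised that reductions in depressive symptoms will be mediated by improvements in insomnia symptoms". Trial objectives adds that "the potential mediating role of cognitive processes, including repetitive thinking, dysfunctional beliefs about sleep and pre-sleep arousal, on treatment effects will be explored". The first is a stated directional hypothesis; the second is exploratory.

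Data collection, management, and statistical methods gives both purpose and method. The purpose is "To determine whether improvements in depression are mediated by changes in sleep". The method is an MMRM "using depression symptoms as the outcome and including a 3-way interaction term", namely time × group × insomnia. For the remaining mediators, "additional MMRM analyses will be used and include 3-way interaction terms (time × group × mediator").

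Under Measures of mechanisms, "All potential mechanisms will be measured at all four assessments (baseline, primary, secondary, and tertiary endpoints) and explored as mediators of change". Table 1 shows insomnia and depression at the same four assessments. The Blinding section names mediators and moderators as separate things to be examined.

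The article mentions no indirect effect, no combination of paths, and no ordering of mediator before outcome.

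**The concern.** Mediation has two parts: condition changes the mediator (path a), and the mediator changes the outcome given condition (path b). The quantity of interest is the indirect effect that the two produce together. A three-way interaction asks whether the effect of condition on depression over time depends on the level of insomnia. That is effect modification.

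The article states both the question and the test, and they do not match, so this is not a detail left to a fuller analysis plan. Two errors could follow. A real pathway through sleep would usually go undetected. And a finding that the app works better for some children than others could be published as evidence of how it works.

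**Working it through.** **Inputs from the protocol.** Planned total 214, equal allocation, 40% attrition to the primary endpoint, α = 0.05 (taken as two-sided), d = 0.41. Completers: 214 × 0.6 = 128.4, so about 64 per arm. The protocol states no figure for the mediation analysis, so there is none to reproduce.

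**Assumptions.** The effect of condition on the mediator (a) is set to 0.41 SD, borrowing the design effect size. The slope b, the mediator autocorrelation (0.5) and the moderation effects are not in the protocol.

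**Step 1: what the coefficient measures.** With G for group, T for time (0 baseline, 1 follow-up) and M for the mediator, the full model is

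Y = β0 + β1G + β2T + β3M + β4GT + β5GM + β6TM + β7GTM.

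The slope of depression on the mediator is then:

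| | Baseline | Follow-up |
|---|---|---|
| Control | β3 | β3 + β6 |
| Sleep Ninja | β3 + β5 | β3 + β5 + β6 + β7 |

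So β7 is the difference between arms in the change of slope. If depression follows the mediator with the same slope b in every cell, β7 = (b − b) − (b − b) = 0. The indirect effect is a × b, for example 0.41 × 0.5 = 0.205 SD, and β7 does not enter it. The coefficient is therefore zero under linear mediation without interaction, whatever the sample size and whatever a and b are. If M is fixed at its baseline value, the term is plain moderation by baseline severity.

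**Step 2: full mediation, no moderation.** Two-occasion simulations with a = 0.41 SD in the beneficial direction, b = 0.5 and no direct effect. The comparator requires both a and b to be significant.

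| | 3-way, change-score form | 3-way, MMRM with time-varying mediator | 3-way, baseline mediator | Joint test of a and b |
|---|---|---|---|---|
| 128 completers | 5.1% | 3.9% | 5.5% | 75.4% |
| All 214 | 4.4% | 5.4% | 4.9% | 92.6% |

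The three-way term rejects at about α in every form. With a = 0.8 and b = 0.6 at 64 per arm it is still about 5%, against about 100% for the joint test.

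**Step 3: moderation, no mediation.** Here a = 0, so nothing is mediated. The rates are how often the three-way term is significant with 64 per arm, when the treatment effect varies with baseline insomnia. Ranges reflect different simulation set-ups, including different values of b; the −0.3 row comes from a single set-up.

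| Moderation effect (SD) | Time-varying mediator in the model | Baseline mediator in the model |
|---|---|---|
| −0.2 | 8–15% | 17–21% |
| −0.3 | 28% | 40% |
| −0.5 | 26–60% | 73–82% |

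If instead the slope on the mediator itself differs between arms by 0.5 (with b = 0.25), the time-varying forms reject in 68% to 79% of trials at 128 completers. The joint test stays at or below about 5% in the moderation-only settings where it was run.

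**The case against.** **The pieces are already there.** For insomnia, path a is the primary analysis. If the planned model is fitted with all lower-order terms (an assumption), it also contains a mediator slope. Combining a baseline-adjusted test of path a with that slope gave 75.5% joint detection at 64 per arm, the same as a separate joint test. A reader might infer that the trial cannot answer its mediation question. The documents do not support that: mediators and outcomes are measured at all four assessments, and only the named test fails. What remains is that the article nowhere says these terms will be read together. With the three-way term in the model, the time × group coefficient is also conditional on a mediator value, so it is not a general direct effect.

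**Interaction belongs in some mediation models.** True: a causal mediation model may include an exposure–mediator interaction. It is one component there and tests neither path a nor the indirect effect. The three-way term need not be banned, but it should not be read alone as mediation.

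**This is secondary or exploratory work.** Largely right. A reader might infer that every mechanism question is confirmatory and would be decided by this test. Only the insomnia-to-depression pathway is a stated hypothesis; the cognitive processes are to be explored. The primary hypothesis, its endpoint and its contrast are untouched.

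**The false-positive rates are soft.** Also right. They rest on moderation effects that the protocol does not give, and the higher rates come from large effects. The baseline-mediator reading also fits poorly with a stated interest in changes in sleep. The direction of the error stands; no single rate should be quoted as its size.

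**Conclusion.** The point holds for the named test. A stated secondary hypothesis, and the exploratory mediator analyses with it, are tied to a coefficient that measures effect modification. That it is zero under linear mediation without interaction is algebra and does not rest on the assumed effect sizes. True mediation would therefore be detected only at about the α rate, and missed about 95% of the time.

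The comparison figure of about 75% depends on a = 0.41 SD, b = 0.5, 64 completers per arm and no confounding of mediator and outcome. The rate at which moderation alone would pass as mediation is conditional: for moderation by baseline insomnia of −0.2 to −0.5 SD, roughly 8–60% with a time-varying mediator and 17–82% with a baseline mediator. It is higher still in the set-up where the mediator slope itself differs by arm.

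This should be fixed before the mediation analyses are run. It does not threaten the primary result or trial conduct.

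**What to change.** Make the mediation test an indirect-effect estimate:

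- Model the mediator on condition, adjusting for baseline mediator and baseline depression.
- Model depression on the mediator and condition, with the same baseline adjustment.
- Report the indirect effect with a bootstrap or causal-mediation interval.
- State a missing-data approach consistent with the intention-to-treat MMRM, since separate complete-case regressions would lose what that model was chosen to provide.
- Add a sensitivity analysis for mediator–outcome confounding, because the mediator is not randomised.

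Preferably the mediator should precede the outcome. Six-week mediator with 3-month depression is one reasonable pairing, although the hypothesis does not itself name a time point. Keep the cognitive mediators labelled exploratory. If the three-way models are kept, describe them as moderation and do not interpret the term alone as mediation.

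The cost is revised wording and a little more analysis work, with no new data. A later outcome would lose some precision if attrition is higher by then; the protocol gives an attrition figure only to the primary endpoint.

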### Monitoring

The current trial will be overseen by a Trial Management Group to supervise the conduct and safety of the trial in accordance with the guidelines on Data Safety Monitoring set by the National Health and Medical Research Council [52]. Parents of participants who report an Adverse Event (AE), which includes severe insomnia symptoms (indicated by a score of 5 on item 6 of the PISI) reported at the tertiary endpoint (9-months post-baseline), will receive a pop-up message in the questionnaire with recommendations to seek support from a health professional for their child. A call-back from a psychologist on the research team will also be offered. Participants who report an AE that includes severe depressive symptoms (indicated by a total t-score ≥ 70 on the RCADS) reported at the tertiary endpoint (9-months post-baseline) will receive a pop-up message in the questionnaire recommending that they tell a trusted adult about how they are feeling and seek help from a health professional. They will be provided with information about where to seek help and informed that we will let their parents know they are having a hard time. An email will be sent to the parent or guardian’s email address informing them of their child’s response with the option of a call-back from the team Psychologist. To examine rates of symptom deterioration, an increase of seven points on the PISI-A will be used as the threshold to indicate reliable symptom deterioration at the primary endpoint. This criterion is based on a α = 0.8 and a SD = 5.4 as recommended by Jacobson and Truax [53] and Byars and Simon [32]. All adverse events and serious adverse events and broader safety monitoring will be documented and reported to the Trial Management Group and to the University of New South Wales Human Research Ethics Committee by the Clinical Trial Manager and reported in the primary outcomes paper. If there are concerns for participant safety, based on (but not limited to) a higher than anticipated rate at one or more of the endpoints, the Trial Management Group may recommend pausing or terminating the trial. The University of New South Wales may audit trial conduct and procedures at any time and this process will be independent of the investigators and the sponsor.

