Each study assessment contains questionnaires in relation to the child participant, with the baseline and 9-month follow-up assessment also containing a diagnostic assessment. Some questionnaires are to be completed by the parent (parent-report) and other questionnaires are to be completed by the child (child-report). Participants will have 14 days to complete the baseline assessment and 7 days to complete all other study assessments and will be sent two reminders (Days 3 and 5). All study assessments can be completed using any Internet-enabled device and include both parent- and child-reported measures. The research team will be available for contact throughout the trial period to participants in case assistance is needed, with research team contact details being provided on the study webpage, the Participant Information Sheet, and at each assessment. However, contact with participants will not be proactive or therapeutic in nature. Participants will be reimbursed $10AUD (electronic gift voucher sent to parents via email) for each study assessment and diagnostic assessment ($60AUD total). Discontinuation of the allocated intervention will occur if the participant withdraws from the trial or if they are no longer able to engage in the intervention due to a change in circumstances (e.g., reside outside Australia).

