### Sample size

The total sample size required for detecting change in the primary outcome at the primary endpoint was calculated to be 214. This was based on using α = 0.05, power = 0.8 to detect a medium between-group effect size (d = 0.41) [17, 22] on child-reported insomnia outcomes. This estimate accounts for an attrition rate of 40% between baseline and the primary endpoint. The effect size parameter used in the power calculation accounts for potential effects of the active control condition, as seen in the adolescent study [17], but is more conservative than the between-group effect size reported in that study (d = 0.41) due to the differences in the delivery format (parent-supported vs. self-directed).

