### Blinding

Regarding participant blinding, all study materials will refer to the interventions being examined as “activities to improve sleep” to conceal Sleep Ninja being the smartphone app used in the trial. This is to prevent participants allocated to the control condition from accessing the Sleep Ninja smartphone app, which is publicly and freely available for download in Australia, during their participation in the trial. While participants will be aware of which activity or information they will be required to use (due to the PISCF and instructions for use provided), they will not be directly informed of their condition allocation (i.e., intervention vs. control) to prevent biases in reporting related to expectancies.

The statistician involved in examining the effects of the conditions of primary and secondary outcomes will not be informed of participants’ specific intervention allocation. Condition allocated will be marked as “Condition A, Condition B” to ensure the statistician remains blinded to participants’ intervention upon primary and secondary analysis of the results. All other potential markers of allocation will be removed from the data analysis file. Upon completion of these analyses, the statistician will be become unblinded when examining mediators and moderators as well as intervention completion rates. This data will only be reviewed by the trial statistician upon completion of the primary and secondary outcomes.

The Chief investigators, trial manager and research assistants will be unblinded to participants’ allocation as they will have access to the Qualtrics data to contact participants if they experience adverse events (see Monitoring below for more information). They will also be responsible for downloading and cleaning the data extracted. The Chief Investigators, Trial Managers, Data Analyst and Research Officers/Assistants will not be involved in data analysis of the primary and secondary outcomes.

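### Both severe-symptom adverse event flags are stated for 9 months only; they should also be derived at 6 weeks and 3 months, with clearer labels

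*Protocol article*

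**What the plan says.** The Monitoring section gives three symptom-based safety criteria and ties each to one visit.

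- Insomnia: "severe insomnia symptoms (indicated by a score of 5 on item 6 of the PISI) reported at the tertiary endpoint", that is, 9 months.
- Depression: "severe depressive symptoms (indicated by a total t-score" of 70 or more on the RCADS), also at 9 months.
- Deterioration: "an increase of seven points on the PISI-A will be used as the threshold to indicate reliable symptom deterioration at the primary endpoint", that is, 6 weeks.

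The first two lead to an on-screen message and the offer of a psychologist's call; for depression there is also an email to the parent. The same section lets the Trial Management Group recommend pausing or stopping the trial, "based on (but not limited to) a higher than anticipated rate at one or more of the endpoints". It adds a general commitment: "All adverse events and serious adverse events and broader safety monitoring will be documented and reported to the Trial Management Group", as well as to the ethics committee and in the primary outcomes paper.

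Table 1 schedules the parent PISI and the parent and child RCADS-25 at baseline, 6 weeks, 3 months and 9 months.

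**The concern.** The two named flags are read only at the last visit, about 33 weeks after the intervention ends, and only in children who still answer then. They say nothing about the two visits nearest the intervention, although the pause provision looks to rates at any endpoint.

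Three details affect how the counts would be read.

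- **Insomnia label.** Under Secondary outcomes, PISI item 6 is sleep duration, and a 5 means less than 5 hours. Insomnia severity is the 0–30 total. A child scoring 5 on each of items 1 to 5 but sleeping 5 hours or more is not flagged as severe.
- **Depression label.** The RCADS-25 has 10 depression and 15 anxiety items. A total t-score could mean the depression subscale or all 25 items. The reporter is not named, although the wording of the on-screen message points to the child.
- **Baseline status.** Eligibility uses PISI items 1 to 5 only and sets no upper limit on item 6 or on the RCADS. A child may enter already meeting a flag, and mixing such children with new cases blurs any difference between arms.

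At stake is the usefulness of the safety report in 10 to 12 year olds, not the efficacy conclusion.

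**Working it through.** **1. The plan's own derived figure.** The Monitoring section bases the seven-point rule on a reliability of 0.8 and an SD of 5.4. The reliable change formula gives 1.96 × 5.4 × √2 × √(1 − 0.8) = 6.69, rounded up to 7. The rule reproduces. The cut-offs of 5 and 70 are stated without derivation.

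**2. Stated thresholds against scheduled data.**

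| Visit | PISI, PISI-A and RCADS-25 collected | Insomnia threshold | Depression threshold |
|---|---|---|---|
| 6 weeks | yes | PISI-A rise of 7 | none |
| 3 months | yes | none | none |
| 9 months | yes | PISI item 6 = 5 | RCADS t-score ≥ 70 |

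Each severe-symptom flag covers 1 of 3 follow-up visits; the scheduled data would support 3 of 3. The seven-point rule has a ceiling: six items scored 0 to 5 give a maximum of 30, so a child starting at 24 or more cannot rise by 7.

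**3. Timing.** Taking 9 months as 39 weeks and 3 months as 13 weeks, the flags are read 39 − 6 = 33 weeks after the intervention ends; the 3-month visit falls 13 − 6 = 7 weeks after it. The first 9-month flag cannot exist until week 39 after the first randomisation. A child randomised in week *t* finishes the intervention in week *t* + 6, so everyone randomised by about week 33 has finished before any such flag could prompt a pause. The length of recruitment is not stated.

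**4. Children answering at 6 weeks.** The Sample size section says: "This estimate accounts for an attrition rate of 40% between baseline and the primary endpoint". So 214 × (1 − 0.40) = 128.4, about 128 children or 64 per arm.

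**5. Later loss among these (assumed; the article gives no figure).** A further 10%, 20% or 30% not answering at 9 months is 12.8, 25.7 or 38.5, so about 13, 26 or 39 children who answered at 6 weeks are never checked against either flag. Children who missed 6 weeks may return later, but that does not change this count.

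**6. Expected flags at 6 weeks (assumed; the article gives no rate).**

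| Assumed rate | Of 128.4 | Per arm (64.2) |
|---|---|---|
| 2% | 2.6 | 1.3 |
| 5% | 6.4 | 3.2 |
| 10% | 12.8 | 6.4 |

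Even zero flags among 64 children would be compatible with a rate of up to 1 − 0.05^(1/64) = 4.6% (one-sided 95% limit).

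**7. Share of ever-flagged children missed by a 9-month reading.** With a rate *p* per visit, independence between visits and full response, the share is 1 − *p* / [1 − (1 − *p*)³]. This gives 66% at *p* = 0.02 and 63% at *p* = 0.10. Symptoms do persist, so the true share should be smaller; if every flag lasted through 9 months, only drop-outs would be missed.

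**The case against.** The best defence is that the 9-month wording mainly governs a response to a child, not a safety table. Holding that response until the last visit fits the section on procedure and participant timeline, where "contact with participants will not be proactive or therapeutic in nature", and avoids a psychologist's call before the 3-month endpoint. This stands as a reason to be careful about responding earlier. It is not a reason to leave earlier data uncounted.

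A reader might infer that safety goes unmonitored before 9 months. The article does not support that. The adverse event wording is not exhaustive, and all events are to be reported. Parents report new diagnoses and treatment at each follow-up. Under Blinding, the unblinded staff's role is explained by the fact that "they will have access to the Qualtrics data to contact participants if they experience adverse events". The pause provision is not confined to rates. Parent PISI and RCADS depression are also secondary outcomes compared between arms, so a child lost before 9 months still contributes earlier scores. But comparisons of means do not count severely affected children, and a parent-reported diagnosis depends on the child having been assessed. The exploratory RCADS cut-off of 65 in the statistical methods is not a safety criterion and reads as a 9-month comparison.

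A by-arm table is the sort of detail an article leaves to an analysis plan, so its absence is no error. The visit at which the flags apply is different: the article states it.

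**Conclusion.** The point holds as a narrow one. The stated rule leaves out a depression threshold at 6 weeks and any symptom threshold at 3 months, although the data are collected and the pause provision covers every endpoint. This is a cheap improvement to safety reporting that should be made.

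Its size is modest: on the assumed rates, about 1 to 6 flagged children per arm at 6 weeks, and 13 to 39 early responders never checked. Only the 40% attrition comes from the article; the later loss and the flag rates are assumptions. The counts support description only.

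Two further inferences would go too far. The RCADS wording is ambiguous, not shown to be wrong, since the article also calls the depression subscale sum a total score. And the pause provision is not contradicted, because it can draw on other information; the named flags simply supply it with a rate at one endpoint of three.

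**What to change.** - Derive both flags at 6 weeks, 3 months and 9 months, and report aggregate rates to the Trial Management Group.
- In the primary paper, tabulate them descriptively by arm and visit, with the number answering as denominator. Separate children who met the flag at baseline from new cases.
- Label the item 6 flag as sleep under 5 h, not as severe insomnia.
- State that the RCADS flag uses the depression-subscale t-score, and name the reporter.
- Keep the seven-point PISI-A rule.

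No new data are needed. The direct cost is one extra table and t-score scoring at two more visits. The harder cost is that deriving flags during the trial shows staff individual children with severe scores. The investigators and the ethics committee must decide in advance how to respond, because an active response at 6 weeks could act as a co-intervention before the 3-month endpoint. Whether to extend the messages, emails and call-backs to earlier visits is for them to decide.
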